## Abstract

**Background:**

The prevalence of physical inactivity among children and adolescents is alarmingly high despite the well-documented and comprehensive benefits of regular physical activity (PA). Therefore, PA promotion should start early in childhood and adolescence. Although reducing recreational screen time in children and adolescents is an urgent concern, digital approaches have the potential to make activity promotion attractive and age appropriate for the target group. KIJANI is a mobile app approach to promote PA in children and adolescents via gamification and augmented reality.

**Objective:**

This study protocol aims to describe the KIJANI intervention in detail, as well as the evaluation approach.

**Methods:**

KIJANI is based on the concept that virtual coins can be earned through PA, for example, in the form of a collected step count. With these coins, in turn, blocks can be bought, which can be used to create virtual buildings and integrate them into the player’s real-world environment via augmented reality. PA of users is detected via accelerometers integrated into the smartphones. KIJANI can be played at predefined play locations that were comprehensively identified as safe, child-friendly, and attractive for PA by the target group in a partner project. The evaluation process will be divided into 2 different stages. The phase-I evaluation will be a mixed methods approach with one-on-one semistructured interviews and questionnaires to evaluate the user experience and receive feedback from the target group. After the implementation of results and feedback from the target group, the phase-II evaluation will proceed in the form of a 2-arm randomized controlled trial, in which the effectiveness of KIJANI will be assessed via objectively measured PA as well as questionnaires.

**Results:**

The study received ethical approval from the ethical board of the Technical University of Munich. Participants for the phase-I evaluation are currently being recruited.

**Conclusions:**

The study will help to determine the efficacy, applicability, and user experience of a gamified activity promotion application in children and adolescents. Overall, digital health approaches provide easy and wide reachability at low cost and are age appropriate and attractive for the target group of adolescents. Strategies have to be developed to apply digital health approaches in the best possible way for activity promotion.

**International Registered Report Identifier (IRRID):**

DERR1-10.2196/55156

## Introduction

Physical inactivity has emerged as a worldwide pandemic, constituting the fourth leading cause of mortality worldwide [1]. A study involving 1.6 million healthy adolescents aged 11 to 17 years revealed that a staggering 81% of healthy youth are not sufficiently physically active [2]. The situation has been further exacerbated by the emergence of the COVID-19 pandemic and its associated restrictions that have further increased physical inactivity among adolescents. According to current analyses, activity levels among healthy youth decreased by 20% during the COVID-19 pandemic [3]. The prevalence of physical inactivity among children and adolescents is alarmingly high despite the well-documented and comprehensive benefits of regular physical activity (PA) including improvements in physical fitness, cardiometabolic health, bone health, cognitive performance, and mental health, among other benefits [4].

Adolescence marks a critical transitional phase during which health habits such as an active lifestyle and future health behaviors are established and manifest [5]. This implies the presence of a tracking effect of PA, whereby the more active a person is during childhood and adolescence, the more likely they are to remain active in adulthood [6,7]. Therefore, PA promotion starting from childhood and adolescence is of immense importance.

Although reducing recreational screen time in children and adolescents is an urgent concern and is strongly recommended by the World Health Organization, the potential of digital technology to make prevention and health promotion attractive and age appropriate for adolescents needs to be recognized [4]. Adolescents are power users of technology, and digital approaches allow them to reach adolescents in their personal environment. To promote PA in the particularly important phase of adolescence, we have developed a digital intervention approach called “KIJANI” that provides new opportunities for promoting and supporting PA. Specifically by targeting children and adolescents, the interdisciplinary project aims to motivate the target group through an app with a game-based concept and augmented reality to engage in PA, especially outdoors [8]. Various studies have demonstrated that gamification in health applications positively influences the behavior of the target audience [8-10] and enables children and adolescents to achieve recommended activity goals in a playful context [11]. Based on a review exploring the potential of augmented reality games for children and adolescents, the fusion of virtual and real-world elements offers promising opportunities to enhance PA and social interaction [12]. Augmented reality integrated into exergames has shown particular appeal among children [13], possibly due to their innate inclination toward play, making children an ideal target audience for gamified activity promotion [9].

This paper describes the KIJANI intervention in detail as well as the study protocol for its evaluation.

## Methods

### KIJANI Intervention

The name KIJANI is Swahili and translates to “green.” It stands as a German abbreviation for “Children & Youth: active, nature-conscious, innovative!” KIJANI is a smartphone app explicitly developed for children and adolescents to increase PA through a gamified approach. The basic game concept is that virtual coins can be “earned” through PA, for example, in the form of a collected step count. These coins can in turn be used to “buy” blocks, which can be used to create virtual buildings and integrate them into the player’s real-world environment via augmented reality, see Figure 1. Using challenge-achievement-reward loops as provided via the coin reward system in KIJANI was shown to increase the desire to play in previous research [14]. PA of users is detected via accelerometers integrated into smartphones and is linked to the KIJANI app on a technical basis.

Earning coins is based on a fitness challenge in the app, for example, consisting of 10,000 steps per day. The achievement of the main goal as well as intermediate goals are rewarded with coins. The main goal of 10,000 steps is rewarded with 50 coins, and intermediate goals, for example, 5000 steps, are rewarded with 20 coins. The blocks differ in price, for example, grass and brick cost 2 coins, water and bookshelf cost 5 coins, and the most expensive is glass and gold with 10 coins. Some blocks such as dirt and stone are free and unlimited to ensure enjoyment for the users. A progress bar in the app shows the individual progress over the course of the day, encouraging participants to reach the daily goal.

KIJANI is designed to be played both alone and with friends in a group. To play together with friends, requests must be sent and confirmed. Then KIJANI can be played together in a group and buildings can be created together. Players can individually specify who can visit, build, and administrate buildings, which ensures that no uninvited players can participate and therefore is another safety issue in KIJANI. In addition, the individual activity behavior can be compared with friends in a ranking list, which is another incentive for PA, see Figure 2. The ranking is also available for nonfriends, as there is a setting to show all players.

**Figure 1 figure1:**
[figure not shown]
An overview of screens in the KIJANI app: KIJANI home screen (left), KIJANI shop to buy blocks (middle), and KIJANI game in augmented reality (right).

**Figure 2 figure2:**
[figure not shown]
The features of the KIJANI app to connect with friends: friends ranking (left) and friends list (right).

KIJANI was developed in cooperation with the research project “WALKI-MUC – Evaluation of physical activity opportunities and walkability perceived by children and youth in Munich,” conducted by the Associate Professorship of Didactics in Sport and Health at the Technical University of Munich. In WALKI-MUC, children and adolescents aged 6 to 17 years (n=93) identified walkable places in Munich (places within walking distance from their homes) that they considered supportive of PA. The participants provided qualitative descriptions of these PA-friendly places through participatory methods such as photovoice, walking interviews, and mapping exercises while researchers tracked the walked routes and GPS locations. Focus group discussions and the one-on-one sharing of the individual significance of these places in interviews provided insights into factors contributing to safety and attractiveness (eg, accessibility and presence of people) at the locations, as perceived by the children and adolescents. The descriptions and locations of these identified PA-friendly places of WALKI-MUC are incorporated into the KIJANI app. KIJANI can only be played in these comprehensively defined, child-friendly locations, ensuring that KIJANI can only be used in a safe and appealing environment for the target group. There is a location search feature implemented in the KIJANI app to find the play locations in the close environment. In addition, the route to the locations is displayed on the map (see Figure 3). This not only encourages users to be active but also supports a healthy lifestyle as extra steps can be accumulated.

At these play locations, a server is created in which KIJANI is played. Multiple servers can be created at 1 play location so that different buildings with different friends can be created at 1 play location. If players want to play in groups, friends have to be invited to the server to ensure that the players are in a safe play environment where no one else can intrude.

**Figure 3 figure3:**
[figure not shown]
The WALKI-MUC map with play locations (left) and the navigation to play locations (right).

### Evaluation Design

It is planned to evaluate the KIJANI app in a 2-phase approach as displayed in Figure 4. The phase-I evaluation will be a mixed methods design, in which the target group evaluates the user experience of the KIJANI app. The phase-II evaluation will be a 2-arm randomized controlled trial (RCT), in which the intervention group (IG) will use the KIJANI app, while the control group (CG) will not use the KIJANI app. Within this second evaluation stage, the effectiveness of KIJANI will be assessed via objectively assessed PA as well as standardized questionnaires.

**Figure 4 figure4:**
[figure not shown]
The evaluation procedure with the phase-I and phase-II evaluations and feedback loop.

### Ethical Considerations

The study protocol has already been approved by the ethical board of the Technical University of Munich (project 2023-185-S-NP). All children and their guardians will provide written informed consent.

For the described evaluation study of KIJANI, a development version of the app is used and distributed through TestFlight. Participants are required to log into the app using pseudonyms to safeguard their data privacy. Throughout app use, step count and GPS location are shared and digitally stored in a firebase. Personal data is processed in accordance with the provisions of the current data protection laws pursuant to Art. 12 (1) BayDSG. Prior to the official release of KIJANI, all necessary international regulations will be considered.

### Participants and Enrollment

Children and adolescents at the age of 10-16 years will be included in this study. Children with walking impairments and cognitive impairments that hinder their ability to understand the task will be excluded from the study.

### Phase-I Evaluation

#### Overview

The primary outcome of the phase-I evaluation is the individual evaluation and feedback on KIJANI by the target population. Study participants will use the KIJANI app for 25 minutes in a group of 3 participants at a KIJANI play location under the supervision of the researcher. For this evaluation design, participants will have enough coins available as the main focus is on the user experience with KIJANI. Researchers ensure that all participants of a group have sufficient time and experience with the app allowing them to give informed feedback at a later stage. Afterward, the app will be evaluated qualitatively with each participant in one-on-one semistructured interviews as well as quantitatively with standardized questionnaires on user experience, PA enjoyment, as well as activity-related self-efficacy.

#### Qualitative Evaluation

In one-on-one semistructured interviews, participants will report on their opinions and experiences with KIJANI. For this purpose, a previously generated interview guide, including mainly open‐ended questions, will be used. The interview guide includes warm-up questions to establish a good relationship with the participants and to inquire about their attitudes toward smartphone use, digital games, as well as PA. The main part of the interview is related to the participants’ opinions on the KIJANI app, including questions about what participants liked and what they would improve in the app. At the end of the interview, participants will have another opportunity to express further comments and ideas. All interviews will be conducted in person, audio recorded, and then transcribed verbatim. Interviewers will not be familiar with the participants prior to study initiation. The interviews will be evaluated by the respective interviewer. For evaluation purposes, categories will be generated guided by a systematic reduction process during data analysis. Text sequences will be classified into suitable categories, and thereby codes will be generated inductively. Possible uncertainties concerning the coding scheme will be discussed by the researchers and homogeneously adjusted. Data collection will proceed until data saturation has been achieved. Data will be considered saturated when recurring codes are observed across various interviews, accompanied by a decreased emergence of new codes during analysis (inductive thematic saturation). The qualitative evaluation process is displayed in Figure 5.

**Figure 5 figure5:**
[figure not shown]
The procedure of the qualitative evaluation process of KIJANI.

#### User Experience

In addition, the user experience with the KIJANI app is evaluated with a user experience questionnaire [15]. User experience thereby summarizes different aspects that are important for the subjective evaluation of a product: usability aspects, joy of use, as well as aesthetic design. The user experience questionnaire consists of 26 bipolar terms (pairs of opposites, eg, annoying and enjoyable), which are evaluated over 7 levels. The items consist of the following 6 domains: effectiveness, transparency, predictability, stimulation, originality, and attractiveness. The questionnaire shows high reliability and construct validity [16].

#### PA Enjoyment

PA enjoyment is evaluated using the short version of the PA Enjoyment Scale (PACES-S). The PACES-S is a measurement tool commonly used in intervention research to measure enjoyment of PA, as it is closely associated with adherence and compliance to PA guidelines [17]. The German version of the PACES is reliable and valid for use in children and adolescents [18]. The short version of the questionnaire consists of 4 items with 5 scales (eg, PA brings me joy). It shows comparable measurement properties to the long version of the PACES and is therefore used in this study [19].

#### Activity-Related Self-Efficacy

Perceived self-efficacy in the context of PA is measured using the German version of the PA Self-Efficacy Scale. The scale consists of 8 items, each of which is answered on a 5-point Likert scale ranging from 1 (“do not agree at all”) to 5 (“fully agree”). The self-efficacy scale for PA measures activity-related self-efficacy with 6 items and activity-related social support from family and friends via the remaining 2 items. The reliability and validity of the German version were shown in a study with 454 schoolchildren [20].

### Phase-II Evaluation

#### Overview

After the implementation of the results of the first evaluation phase, the second evaluation in the form of an RCT will be conducted. The IG will use the KIJANI app in their everyday life over a period of 2 weeks, while the CG sticks to their normal everyday life without using the KIJANI app. Randomization will be 2:1 into IG and CG, with the randomization process clustered by age and gender to ensure equal distribution in the groups. The phase-II evaluation sample size was calculated with G*power (2-sided α of 0.05, power 0.9). A sample of 62 participants is planned for this study. Of these, 41 participants will be assigned to the IG and 21 participants will be assigned to the CG. After completion of the study, the CG will also have the opportunity to use the KIJANI app.

The primary outcome of the phase-II evaluation is the everyday PA of the children and adolescents. PA is objectively recorded in the form of daily step count via accelerometers integrated into the smartphone over the entire study period in IG and CG. Through the KIJANI intervention, we hope to increase the PA of children and adolescents by 10%.

Secondary end points are health-related quality of life, activity-related self-efficacy, PA enjoyment, as well as the user experience with the app. The last 3 will be investigated as described above in the phase-I evaluation. Secondary end points will be assessed before and after the intervention period.

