### Statistical Methods

The data analysis will involve both descriptive and analytical analyses. Initially, descriptive analysis will focus on the sociodemographic characteristics of the study population. Normal distribution of the data will be tested with the Shapiro-Wilk test. In terms of dropouts, intention-to-treat analysis will be performed using multiple imputations, to be able to calculate with a complete data set. To capture the longitudinal development of the activity level throughout the study period, a linear mixed model will be used to compare the change of the PA behavior over time between IG and CG. To investigate differences between the groups in activity-related self-efficacy, health-related quality of life, and PA enjoyment, these will be compared with 2-tailed *t* test or Mann-Whitney *U* test as appropriate depending on the distribution of the data. All analyses will be performed with RStudio (version 4.1.2; RStudio Team), with the level of significance set to 2-sided *P* values <.05 for all tests. RStudio was used for its tailored integration with the R programming language, providing an efficient and organized environment for reproducible data analysis, visualization, and documentation in our scientific study.

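### Randomisation is balanced by age and gender, but the two-sample tests fixed for three secondary end points ignore both factors and are conservative if those factors are prognostic

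*Protocol article*

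**What the plan says.** Phase-II Evaluation, Overview: "Randomization will be 2:1 into IG and CG", "with the randomization process clustered by age and gender to ensure equal distribution in the groups". "A sample of 62 participants is planned for this study", and "41 participants will be assigned to the IG and 21 participants will be assigned to the CG".

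Statistical Methods: for the primary outcome, daily steps, "a linear mixed model will be used to compare the change of the PA behavior over time between IG and CG". Covariates are not mentioned. For activity-related self-efficacy, health-related quality of life and physical activity enjoyment, the groups are compared by a two-tailed t test or a Mann-Whitney U "test as appropriate depending on the distribution of the data". Nowhere does the article say that age or gender enters any analysis.

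**The concern.** Balancing the arms on age and gender takes the variation due to those factors out of the difference between arms. A two-sample test does not know this. It still counts the spread between younger and older children, and between boys and girls, as random error. Its standard error then describes a trial without balancing, and it exceeds the true variability of the estimate whenever the factors are prognostic. Intervals come out too wide and p-values too large.

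The secondary end points would lose some of the precision that the design has already secured. For these end points the tests are named in the text, so this is a stated choice and not a detail left open.

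**Working it through.** **The plan's own figure.** "The phase-II evaluation sample size was calculated with G*power (2-sided α of 0.05, power 0.9"), giving 62. No standard deviation, standardised effect or test family accompanies it; the only target is "we hope to increase the PA of children and adolescents by 10"%. The 62 can therefore be neither confirmed nor refuted. Solving backwards with the noncentral t distribution, 41 and 21 children give 90% power, two-sided, at a standardised difference d = 0.884. The alternatives would be 0.794 one-sided, or 0.837 with 31 per arm. The calculation below takes the arm sizes as given and does not depend on which was meant.

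**Inputs from the article.** 62 children, 41 and 21, ratio 2:1, two-sided 5%.

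**Assumptions.** Two age bands by gender (4 strata), permuted blocks of 3, total outcome SD of 1, and a share R² of outcome variance explained by age and gender together, from 0 to 30%. The article gives none of these.

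**Formula.**
- Standard error reported by the t test: √(1/41 + 1/21) = √(0.0244 + 0.0476) = 0.268, whatever R² is.
- True SD of the estimate under perfect balance: √(1 − R²) × 0.268. At R² = 0.20 this is 0.894 × 0.268 = 0.240.
- The reported error is therefore too large by the factor 1/√(1 − R²), which is 1.118 at R² = 0.20.

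**Simulation**, 20,000 trials per setting. Balance is slightly imperfect because the last block in a stratum may be incomplete, so the effect is a little smaller than the formula gives. The adjusted analysis is a linear model with arm, age band and gender.

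| R² | Reported SE (t test) | True SD | SE too large by | Type I error, t test | Type I error, adjusted | Coverage of 95% interval, t test |
|---|---|---|---|---|---|---|
| 0 | 0.268 | 0.268 | 0% | 4.9% | 4.9% | 95.1% |
| 5% | 0.268 | 0.263 | 2% | 4.5% | 5.0% | 95.5% |
| 10% | 0.269 | 0.257 | 5% | 4.0% | 5.2% | 96.0% |
| 20% | 0.269 | 0.243 | 11% | 3.0% | 5.0% | 97.0% |
| 30% | 0.269 | 0.226 | 19% | 2.0% | 4.8% | 98.0% |

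**Power.** At d = 0.8 the exact power of the t test with 41 and 21 and no prognostic factor is 83.5%. Simulated power at R² = 0, 5, 10, 20 and 30%:
- t test: 83, 84, 84, 86 and 87%
- adjusted: 83, 85, 86, 91 and 94%
- gain, from repeated runs: about 0, 1, 2.5, 4.5 and 6.5 points

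At d = 0.884, where power is nearer its ceiling, the gains are about 0, 1, 2, 3 and 4 points.

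The Mann-Whitney test was not simulated. It cannot carry the factors either.

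**The case against.** **The size is not known.** Nothing in the article says how strongly age or gender predicts these questionnaire scores. The end points are measured before and after the intervention, and the article does not say whether final values or changes are compared. If changes are compared, stable age and gender differences largely cancel and R² may be near zero. This stands, and it is why the range starts at 0.

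**The error is on the safe side.** The t test never exceeds its nominal 5%, and its power does not fall below what it would have without stratification. Only secondary end points are affected, and no power is claimed for them. This also stands: the cost is a forgone gain and not a loss of validity.

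A reader might infer three stronger points that the documents do not support.

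- *That the primary analysis has the same fault.* The article is silent on covariates in the mixed model, and a condensed article commonly leaves these to the full protocol or analysis plan. The stated contrast is also change over time. With a random intercept per child and complete data, time-constant age and gender main effects do not sharpen it. In 40 simulated trials of 62 children over 14 days, with the factors explaining 30% of between-child variance, the standard error of the group-by-time term was 0.01780 both with and without them.
- *That whole age-gender groups are allocated*, which would invalidate independent-sample tests. The stated purpose, equal distribution, points to stratification, so this is a slip of wording.
- *That strata are single years of age by gender*, giving very small cells. The article defines neither age bands nor blocks.

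**Conclusion.** The point holds for self-efficacy, quality of life and physical activity enjoyment. The design balances on two factors that the named tests cannot use. If age and gender explain 10 to 30% of outcome variance, the standard errors are about 5 to 19% too large, and about 2.5 to 6.5 points of power at d = 0.8 are left unused. At 5% the loss is about 1 point, and at 0 there is none.

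These sizes rest on the assumed R², four strata, blocks of 3 and normally distributed outcomes. The direction needs only that allocation is balanced on the factors and that they are prognostic. The tests are conservative, so a positive result would not be put in doubt. No defect in the primary model is shown.

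**What to change.** - In the randomisation text, replace *clustered* by *stratified*.
- In Statistical Methods, replace the t test and Mann-Whitney comparisons of the three secondary end points by a linear model (ANCOVA) with arm and the age and gender factors, coded as in the randomisation.
- Name the same two factors in the primary mixed model, so that all analyses follow the design. This is for consistency; no gain in precision is claimed for the change-over-time contrast.

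The cost is a few lines of text and two model terms. Residual degrees of freedom fall from 60 to 58, which moves the critical t value only from 2.000 to 2.002. Even if the factors predict nothing, power is practically unchanged (89.5% against 89.4% at d = 0.884). No further participants or data are needed. Phase II follows phase I, which the article reports as still recruiting, so on that timetable the change can be specified before any phase II data exist.

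### Phase-II steps are counted by the phone, and only the intervention arm is rewarded for phone-counted steps, so a positive primary result could reflect phone-carrying as well as activity

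*Protocol article*

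**What the plan says.** The Overview of the Phase-II Evaluation defines the endpoint: "The primary outcome of the phase-II evaluation is the everyday PA of the children and adolescents". It then fixes the instrument: "PA is objectively recorded in the form of daily step count via accelerometers integrated into the smartphone", for both arms and the whole study period. The hoped-for gain is 10%.

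The section on the KIJANI Intervention shows that the game runs on the same kind of signal: "PA of users is detected via accelerometers integrated into smartphones and is linked to the KIJANI app on a technical basis". Rewards follow from it. "Earning coins is based on a fitness challenge in the app, for example, consisting of 10,000 steps per day", and "The main goal of 10,000 steps is rewarded with 50 coins, and intermediate goals, for example, 5000 steps, are rewarded with 20 coins". A progress bar shows the day's progress, and "the individual activity behavior can be compared with friends in a ranking list, which is another incentive for PA".

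The comparison arm has none of this: "the CG sticks to their normal everyday life without using the KIJANI app".

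Statistical Methods plans a linear mixed model for change in activity over time between arms, with multiple imputation for dropouts. For phase II, the Limitations section names one bias, the Hawthorne effect, and describes it as activity that may be higher than usual during the two weeks.

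**The concern.** The endpoint is meant to be everyday physical activity. What is measured is activity that happens while the phone is on the body. The intervention is intended to change the first, but it also gives IG children a direct reason to change the second, since a step taken without the phone earns no coins and no rank. Play itself also happens on the phone at outdoor locations. CG children have no matching reason.

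The likely error therefore differs by arm and favours the app. The usual safeguards do not remove it:

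- Randomisation balances carrying habits at entry, but this change comes after randomisation.
- Intention-to-treat analysis keeps the arms intact but does not correct the measurement.
- Imputation is stated for dropouts, not for steps the phone did not record.
- Comparing change over time cancels stable habits, but not a change in carrying that starts with the app.

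Objective recording does avoid the recall and reporting bias that the Discussion criticises in earlier studies. It does not avoid this one. What is at stake is whether a positive primary result can be read as more physical activity.

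**Working it through.** **Inputs from the protocol article.** Target increase 10%; 62 participants, 41 IG and 21 CG; two-sided α 0.05; power 0.90 (Phase-II Evaluation, Overview). No figure is given for the share of steps taken with the phone on the body, for the mean step count or for its SD. Every value used for these below is an assumption.

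**The plan's own figure.** The 62 cannot be rebuilt forwards, because the article gives no effect size or SD. Solved backwards with a two-sided two-sample t test, 41 against 21 at 90% power corresponds to a standardised difference of 0.884. If that difference stands for the 10% target, the SD is 10/0.884 = 11.3% of the mean. This is used only in the last step.

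**Step 1: the relation.** Let *c* be the share of true steps taken while carrying the phone. Then recorded steps = true steps × *c*, and

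apparent ratio (IG/CG) = true ratio × (c_IG / c_CG).

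For change from baseline, with equal carrying in the arms beforehand and a shift in the IG when the app starts, the ratio of changes reduces to the same expression.

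**Step 2: no true change (true ratio 1).**

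- 60% in CG, 66% in IG: 0.66/0.60 = 1.10, an apparent +10%.
- 60% in CG, 70% in IG: 0.70/0.60 = 1.167, an apparent +17%.

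**Step 3: how much carrying must rise to give +10%.** The rise needed is 0.10 × *c*. The last column assumes a 14-hour waking day with steps spread evenly, so minutes = rise × 14 × 60.

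| CG share | IG share needed | Rise (points) | Extra minutes per day |
|---|---|---|---|
| 0.50 | 0.55 | 5 | 42 |
| 0.60 | 0.66 | 6 | 50 |
| 0.70 | 0.77 | 7 | 59 |
| 0.80 | 0.88 | 8 | 67 |
| 0.90 | 0.99 | 9 | 76 |

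**Step 4: why a positive result is ambiguous.** A recorded +10% fits a true ratio of 1.10 with equal carrying. It fits a true ratio of 1.00 with a carrying ratio of 1.10. It also fits any mixture, such as a carrying ratio of 0.735/0.70 = 1.05 and a true ratio of 1.10/1.05 = 1.048. Recorded steps alone cannot tell these apart.

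**Step 5: chance of a significant result with no true change.** Two-sided t test, 41 against 21, as a stand-in for the planned mixed model; nominal rate 5%.

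| Share, CG to IG | Apparent effect | SD 11.3% of mean | SD 30% of mean |
|---|---|---|---|
| 0.70 to 0.735 | +5.0% | 37% | 9% |
| 0.70 to 0.75 | +7.1% | 64% | 14% |
| 0.70 to 0.77 | +10.0% | 90% | 23% |

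The rejection rate depends heavily on the SD. The bias in the point estimate does not.

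**The case against.** The strongest reply is that the article shows a possibility and not a size. It gives no carrying shares; 60% and 66% are chosen because they give the target exactly. The planned analysis compares change over time, and how a shift in carrying enters it depends on the baseline and the time coding, which the article does not set out. The high rejection rates need an SD near 11% of the mean. All of this stands, and it limits what can be said about magnitude.

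A second reply is that carrying instructions, rules for valid days and sensitivity analyses are commonly left to a full protocol or analysis plan, which is not shown. That also stands, and their absence is not the point here. The point rests on what the article does fix: the instrument, and a reward on that instrument's readings in one arm. Even identical carrying instructions would leave the reward one-sided.

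A third reply is that the obvious statistical repairs are unsound. Excluding days with little carrying, or dividing steps by carried hours, conditions on something that arises after randomisation and that activity itself affects. A child who walks in more hours of the day will appear to carry the phone longer. Such rules could remove a real effect or drop different kinds of days in each arm. This is right, and neither should be used as the correction.

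Two further inferences are tempting but unsupported. A reader might assume that days with the phone left on a table are stored as low-activity days; the article does not say how such days are handled. A reader might also suppose that children would shake the phone to earn coins; nothing in the article bears on this.

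**Conclusion.** The concern holds as a measurement bias that can differ by arm. The article makes phone-recorded steps the primary outcome and rewards phone-recorded steps in the IG only, and its limitations do not mention the consequence. On the assumed shares, a rise in carrying of 5 to 9 percentage points in the IG alone would reproduce the full 10% target with no change in activity.

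A reader might go further and conclude that the effect would be an artefact, or that a positive result could not reflect more activity at all. The documents do not support that. They do not show that carrying will change or by how much, and a real effect may be present alongside any artefact. The supportable conclusion is that a positive result, under the design as described, would be ambiguous between more activity and more carrying. Because this touches the meaning of the primary result, it should be dealt with before phase II begins; the article reports that phase I is still recruiting.

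**What to change.** 1. Give both arms the same instruction, from the start of measurement, to carry the phone on the body during waking hours.
2. Record carrying in both arms, for example by a one-line daily self-report, or by hours derived from the phone if the data allow it. Report it by arm next to the primary result.
3. State the primary conclusion in terms of phone-recorded steps unless carrying is similar in the two arms.
4. Name this bias in the limitations as a possible difference between arms, separate from the Hawthorne effect.
5. Keep all days in the primary analysis. Label any restriction to valid days, or any analysis of steps per carried hour, as a sensitivity analysis only, for the reason given above.

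The cost is a short instruction, a small daily burden on participants, and a slight departure from the CG's usual routine. The carrying record is itself imperfect: self-report can be coloured by arm, and phone-derived hours cannot separate a child sitting still from a phone left on a table. Some bias will remain, since the reward stays in one arm. An independent body-worn accelerometer in both arms, at least in a subsample, would go further towards separating carrying from activity, at the price of extra devices; the steps above do not depend on it.
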